##### Saint George’s Respiratory Questionnaire (SGRQ)

The SGRQ addresses aspects related to three domains: symptoms, activity, and psychosocial impacts that respiratory disease inflicts on the patient. Each domain has a maximum possible score; the points for each answer are added up and the total is referred to as a percentage of the maximum. A total score is calculated from 0 (no health impairment) to 100 (maximum health impairment). In addition to the total score, there is also a score for each domain of symptoms, activity, and impact, which are also scored from 0 to 100. Values above 10% reflect an altered QOL in that domain. Changes equal to or greater than 4% after an intervention, in any domain or the total number of points, indicate a significant change in the patients’ QoL [35].

The SGRQ will be used to assess QoL, which will be analyzed in Phase I and at the ends of Phase II and Phase III.

##### London Chest Activity of Daily Living (LCADL)

The London Chest Activity of Daily Living (LCADL) scale has four domains (personal care, household activities, physical activities, and leisure activities), with 15 questions in total, to assess the limitations to ADLs in patients with COPD [36]. Each question in the domains receives a score from 0 to 5, indicated by the patient, with the highest value representing the maximum inability to perform ADL due to dyspnea. The total score can range from 0 to 75 points, and the higher the value, the greater the limitation in ADL. The scale also has question 16, which refers to a specification of ADL impairment due to dyspnea, in any situation, and the patient must answer this question by ticking one of the three alternatives: “a lot”, “little”, or “not at all” [37].

The LCADL will be used to assess ADLs, which will be analyzed in Phase I and at the ends of Phase II and Phase III.

##### Six-Minute Walk Test (6MWT)

To evaluate functional performance, the 6MWT will also be applied according to the recommendations of the American Thoracic Society [38]. The test will be performed in a 30 m corridor, on a flat surface on which the subjects will be instructed to walk as fast as possible, without running, for six minutes. The subject will be allowed to rest during the test and resume walking as soon as they are able. During the walk, the examiner will give verbal stimuli every minute, always using the same tone of voice and the standardized phrase: “you are doing very well”. The subject will be instructed to interrupt the test if he presents pain in the lower limbs, tachycardia, dizziness, or any other symptom of discomfort. Immediately before and after the test, systemic blood pressure (BP), heart rate (HR), oxygen saturation (SpO2), and level of dyspnea and lower limb fatigue (Borg scale) will be measured. Two tests will be performed with an interval of 30 min between them, and the test in which the patient has walked the longest distance will be used for analysis. If the difference in the distance walked between the two tests is greater than 10%, a third test will be performed [38,39]. It is noteworthy that a mean increase of 30 m in 6MWT covered distance after pulmonary rehabilitation in COPD patients indicates a minimal clinically important increase [39,40].

The 6MWT will be used to evaluate functional performance; therefore, it will be evaluated in Phase I and at the ends of Phase II and Phase III.

##### COPD Assessment Test (CAT)

The CAT is composed of eight items, called cough, phlegm, chest tightness, shortness of breath, limitations in household activities, confidence in leaving home, sleep, and energy. For each item, the patient chooses only one answer option, the score of which varies from zero to five. At the end of the test, all response scores are added up, and the clinical impact of COPD is evaluated according to the stratification score of the CAT development and validation study [41]. The results vary according to the range of scores obtained, being classified for clinical impact as follows: 6–10 points, mild; 11–20, moderate; 21–30, severe; and 31–40, very severe [42].

The CAT will be used to assess the impact of COPD on patients’ lives, which will be analyzed in Phase I and at the ends of Phase II and Phase III.

### 2.7. Ethics

Each patient will receive information about the purpose and structure of the research and written consent will be required through the Free and Informed Consent Form (ICF) to participate in the study. Patients may opt out of the study at any time before or during implementation of the protocol.

The project has been approved by the Ethics and Research Committee of the Federal University of Jequitinhonha and Mucuri Valleys (reference number 5.274.273).

### 2.8. Analyses

Statistical analysis will be performed following the intention-to-treat principle. Data will be analyzed using the SPSS Statistics statistical package (v.22.0; IBM Corp, Armonk, NY, USA). The normality of the data will be verified using the Kolmogorov-Smirnov test and the homoscedasticity of the data through the Levene test. The parametric data will be expressed as mean and standard deviation. In the case of nonparametric data, the median and its upper and lower limits will be expressed. The data will be analyzed using generalized linear mixed-effects models for repeated measures with post hoc Bonferroni analysis for correction. For all tests, an alpha of 5% will be adopted. Effect sizes will be interpreted based on their minimal clinically important differences (MCIDs).

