### 2.2. Patients

Patients with a clinical diagnosis of COPD who meet the inclusion criteria will be recruited from the waiting list of the Federal University of the Jequitinhonha and Mucuri Valleys (UFVJM) Physiotherapy school clinic, as well as in doctors’ offices and hospitals and through pamphlets and advertisements on local radio.

Patients will be aware that they will be randomized into one of two groups. Group I will receive AT and Group II will be without AT–we chose a control group without any intervention in order to analyze the isolated effect of AT. At the end of the project, if the results are favorable, patients in the control group will be offered the possibility of receiving AT.

The sample size was estimated using the GPower^®^ program (Franz Faul, Universitat Kiel, Kiel, Germany), version 3.1.9.2. For this, a priori analysis was used, considering the t-test for comparisons between groups, for the quality-of-life variable evaluated by the Saint George Respiratory Questionnaire (SGRQ)-Total score [22]. Thus, considering an effect size of 0.59 [22], power of 0.80%, and alpha error of 5%, the sample size was estimated at 50 patients for each group, totaling 100 patients. These calculations assumed a 20% loss in the worst-case scenario.

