#### Treatment of Lost Data (Missing Data)

Missing data will be classified as missed and nonrandom (PNA) when dropouts are due to a lack of efficacy and adverse effects and as missed completely by chance (PCA) when a loss to follow-up does not depend on observed or unobserved measures (e.g., patient moves to another city for non-health reasons). We are planning to perform mixed-effects models for repeated measures (repeated-measures ANOVA) to deal with missing data due to PCA and use single imputation methods (such as best- or worst-case imputation, i.e., assigning the worst possible value of the result for dropouts for a negative reason–treatment failure and the best possible value for positive dropouts (cures)) when considering the absence a PNA. We are planning sensitivity analyses to assess whether the methods used to deal with missing data produce any important differences in the results [43].

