Our work predicts a score of 8 on the PEDro scale as we plan to specify eligibility criteria, randomly assign patients, and use veiled subject allocation by a researcher designated exclusively for this role during research planning, performed using a computer program; we will have well-defined inclusion and exclusion criteria ensuring similar groups with regard to the most important prognostic indicators at baseline; and there will be blinding of the evaluators who will measure the outcomes. Furthermore, we will aim to ensure patient adherence, ensuring that measurements of at least one key outcome will be obtained in more than 85% of subjects initially distributed among the groups, using weekly telephone calls made to patients in the control group; data will be analyzed by intent to treat; we will describe the results of intergroup statistical comparisons in at least one key result; and we will describe measures of precision as measures of variability for at least one key outcome. We will lose in points that do not apply to studies with acupuncture, i.e., blinding of subjects and blinding of the therapist who will apply the therapy. In addition, we will follow up for a total of 16 weeks by reapplying the tests and questionnaires at 8 weeks, which will enable assessment of the responses in the short and long term, which, according to our previous review, has not yet been undertaken.

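### The missing-data text equates the mixed-effects model with repeated-measures ANOVA, and baseline SGRQ is given no stated role in the analysis

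*Protocol article*

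**What the plan says.** Section 2.8 names the analysis principle, "Statistical analysis will be performed following the intention-to-treat principle", and the class of model: "The data will be analyzed using generalized linear mixed-effects models for repeated measures with post hoc Bonferroni analysis for correction". It lists no fixed effects, covariates, contrast or primary visit.

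The subsection Treatment of Lost Data sorts losses into those completely at random (PCA) and those not at random (PNA). For the first it says: "We are planning to perform mixed-effects models for repeated measures (repeated-measures ANOVA) to deal with missing data due to PCA". For the second it will "use single imputation methods (such as best- or worst-case imputation". Sensitivity analyses on the missing-data methods are also planned.

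On timing, the SGRQ subsection says: "The SGRQ will be used to assess QoL, which will be analyzed in Phase I and at the ends of Phase II and Phase III". That gives one baseline and two follow-up measurements, at weeks 8 and 16. Section 2.3 places randomisation after the initial evaluation, so the first SGRQ score is a true pre-randomisation baseline.

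**The concern.** The bracketed term treats two different methods as one. A mixed model fitted by likelihood uses all the visits that each patient attended, and is valid for data missing completely at random (and under the weaker assumption of missing at random). Classical repeated-measures ANOVA needs a full set of visits per patient and removes anyone with a gap. It therefore cannot do the job that the sentence gives it, and deleting randomised patients would sit badly with intention to treat. The imputation does not close the gap, because it covers only the PNA losses, while the PCA losses are the ones left to this model. The named software runs the two methods as separate procedures, so an analyst could follow the text in good faith and run either.

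The second matter is baseline. Every randomised patient will have a pre-randomisation SGRQ score, and the text does not say whether it is a covariate, a response at the first visit, or unused. The choice changes the precision of the primary comparison without any new data.

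**Working it through.** **Inputs from the documents.** Section 2.2 plans the trial by "considering the t-test for comparisons between groups, for the quality-of-life variable evaluated by the Saint George Respiratory Questionnaire (SGRQ)-Total score", with d = 0.59, power 0.80 (printed with a percent sign), alpha 5%, 50 patients per arm and 20% loss. Sidedness is not stated; two-sided is used here.

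**Inputs assumed.** The correlation rho between baseline and follow-up SGRQ is not in the documents; 0.5 to 0.7 is used as the main range. Whether 0.59 is scaled to the raw-score SD or the change-score SD is not stated either, so both are shown.

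**Step 1: the plan's own figure.** A two-sided two-sample t-test (noncentral t) with d = 0.59 needs 47 evaluable patients per arm, and 47 / 0.8 = 58.75, so 59 with 20% loss. The stated 50 does not reproduce as a loss-inflated number; that is a separate point. Here it only fixes the starting position: 50 x 0.8 = 40 completers per arm, and an unadjusted follow-up comparison then has 74.1% power.

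**Step 2: role of baseline, 0.59 on the raw-score SD.** The variance of the group contrast, relative to a follow-up-only comparison, is:
- baseline as a response, group-by-time contrast: 2(1 - rho)
- baseline as covariate: 1 - rho²

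The effective d is 0.59 divided by the square root of that factor. Power at 40 per arm:

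| rho | group-by-time, baseline as response | baseline as covariate | gain |
|---|---|---|---|
| 0.5 | 0.59/√1.00 = 0.590; 74.1% | 0.59/√0.75 = 0.681; 85.3% | 11.2 points |
| 0.6 | 0.59/√0.80 = 0.660; 83.0% | 0.59/√0.64 = 0.738; 90.3% | 7.3 points |
| 0.7 | 0.59/√0.60 = 0.762; 92.0% | 0.59/√0.51 = 0.826; 95.4% | 3.4 points |

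Outside that range the gain is about 15 points at rho 0.4 (66.2% to 81.1%) and under 1 point at rho 0.8 (98.5% to 99.1%).

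**Step 3: 0.59 on the change-score SD.** The group-by-time contrast is then the change-score comparison itself, at 74.1% whatever rho is. Covariate adjustment reduces the variance by (1 - rho²) / [2(1 - rho)] = (1 + rho)/2 = 0.75, 0.80, 0.85. The effective d is 0.681, 0.660, 0.640 and power is 85.3%, 83.0%, 80.7%.

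**Step 4: cost of listwise deletion if classical ANOVA were run.** Illustrative pattern per arm: 40 complete, 5 without week 16, 5 with baseline only, all completely at random. Other settings: compound symmetry, baseline as an unconstrained response, 0.59 on the raw-score SD, normal approximation (hence 75.1% rather than 74.1% at rho 0.5).

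| rho | listwise, either visit | mixed model, week 16 | mixed model, week 8 |
|---|---|---|---|
| 0.5 | 75.1% | 77.7% | 80.9% |
| 0.6 | 83.9% | 85.8% | 88.5% |
| 0.7 | 92.6% | 93.7% | 95.4% |

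The loss is 2.6, 1.9 and 1.1 points at week 16, and 5.8, 4.6 and 2.8 points at week 8.

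**Step 5: is a constrained baseline equivalent?** With both arms sharing one baseline mean, the same calculation on the 40 complete patients gives 86.1%, 91.0% and 95.9%. This is in line with covariate adjustment (85.3%, 90.3%, 95.4% by the t distribution), so either form will serve.

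**The case against.** The strongest reply is that this is a condensed article. Section 2.8 gives a class of model, and covariate lists are commonly left to the full plan. That stands: a reader might infer that the model ignores baseline, but the text neither includes nor excludes it. A repeated-measures model over the three SGRQ visits would most naturally carry baseline as a response, in which case baseline is used. For the same reason, 74% rising to 95% is not a fair statement of the gain. The 74% belongs to an unadjusted follow-up comparison, which the article uses for sample size and not as its analysis; the fair comparator is the group-by-time column above.

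A reader might also infer that patients with a missing visit will be dropped. No sentence says so. The named model keeps partial data, PNA losses are imputed, and sensitivity analyses are planned. Deletion follows only if the bracketed method is the one run, and the loss of power is then modest.

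A third tempting reading is that the test would be a group main effect averaged over all three visits, including baseline, where the true effect is zero. That would have about 49% to 57% power (rho 0.7 to 0.5), but nothing makes it the primary test; post hoc Bonferroni comparisons fit a group-by-time or per-visit contrast equally well.

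Finally, the Discussion credits eligibility criteria with "ensuring similar groups with regard to the most important prognostic indicators at baseline". Such criteria cannot guarantee balance, but the remark belongs to a forecast of a quality score and sets no analysis rule.

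What the reply does not remove is the bracketed term. It is a positive statement, and it is wrong for the purpose given.

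**Conclusion.** The point holds as a wording error with a practical consequence. The lost-data subsection equates two methods that treat incomplete patients differently, and one of them would defeat both the stated purpose and intention to treat. Alongside it, baseline SGRQ has no stated role, and giving it one is a free improvement, not the correction of a stated exclusion.

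The size is moderate and rests on assumptions. On the raw-score scale, covariate adjustment is worth about 11 points of power at rho 0.5, falling to 3 at rho 0.7. On the change-score scale it lifts power from 74% to between 85% and 81%, so under these assumptions it restores the planned 80% after a 20% loss. The 1 to 3 point (week 16) and up to 6 point (week 8) costs of listwise deletion belong to one invented dropout pattern, with every loss completely at random; losses classed as PNA would be imputed and not deleted.

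**What to change.** - In the lost-data subsection, delete the bracketed reference to repeated-measures ANOVA.
- State a likelihood-based linear mixed model for SGRQ total, using all available post-baseline visits (weeks 8 and 16), with group, visit, group x visit, baseline SGRQ total and baseline x visit as fixed effects. A constrained-baseline model is an acceptable equivalent.
- Name the visit at which the between-group difference, with its 95% confidence interval, is the primary estimate.
- Use the same form, each with its own baseline, for the other continuous outcomes measured at both follow-up visits. Body composition by DEXA has a single follow-up, at the end of Phase III, so it needs no visit terms.

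The cost is wording only. The data, the visits and the software stay as planned, and the change is best made before analysis begins.

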#### Treatment of Lost Data (Missing Data)

Missing data will be classified as missed and nonrandom (PNA) when dropouts are due to a lack of efficacy and adverse effects and as missed completely by chance (PCA) when a loss to follow-up does not depend on observed or unobserved measures (e.g., patient moves to another city for non-health reasons). We are planning to perform mixed-effects models for repeated measures (repeated-measures ANOVA) to deal with missing data due to PCA and use single imputation methods (such as best- or worst-case imputation, i.e., assigning the worst possible value of the result for dropouts for a negative reason–treatment failure and the best possible value for positive dropouts (cures)) when considering the absence a PNA. We are planning sensitivity analyses to assess whether the methods used to deal with missing data produce any important differences in the results [43].

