## 1. Introduction

Chronic obstructive pulmonary disease (COPD) is a preventable and treatable respiratory disease characterized by the presence of chronic airflow obstruction that is not fully reversible [1] and by the presence of systemic oxidative stress and inflammation biomarkers [2,3]. Studies on the prevalence of COPD suggest that around a quarter (¼) of adults aged 40 years and older have moderate airflow obstruction [4].

Although COPD compromises the lungs, it also has significant systemic consequences [1,4,5,6]. COPD patients often adopt a sedentary lifestyle that can precipitate the onset of muscle deconditioning through inactivity and a cycle of clinical deterioration [1,7,8,9], negatively impacting the quality of life of patients with COPD [1,10]. Thus, although these patients maintain activities of daily living (ADL) related to self-care, mobility, food, and personal hygiene, their ADLs are considered to be of lesser intensity when compared to healthy individuals [11]. The same is true for physical activity as COPD patients often maintain lower levels of physical activity, according to international guidelines for maintaining physical health [7,8].

The concept of quality of life (QoL) refers to objective and, to a greater extent, subjective indicators of happiness and satisfaction [12]. According to the World Health Organization, QoL is defined as “an individual’s perception of their position in life in the context of the culture and value system in which they live, and in relation to their goals, expectations, standards, and concerns” [13]. In this sense, the administration of questionnaires to assess the HRQoL of patients with COPD has been widely used, generating reliable, valid, and reproducible evidence [14,15].

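### Setting non-random dropouts to the ends of the SGRQ scale lets a few patients erase or create the treatment effect, in either direction

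*Protocol article*

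**What the plan says.** The Treatment of Lost Data paragraph in section 2.8 of the Protocol article sorts missing data into two classes by the reason for loss.

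- **Non-random (PNA).** Data are "classified as missed and nonrandom (PNA) when dropouts are due to a lack of efficacy and adverse effects". The only handling named is to "use single imputation methods (such as best- or worst-case imputation, i.e., assigning the worst possible value of the result for dropouts" with a negative reason, and "the best possible value for positive dropouts (cures").
- **Completely at random (PCA).** Here the plan is "mixed-effects models for repeated measures (repeated-measures ANOVA) to deal with missing data due to PCA".

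The next sentence adds: "We are planning sensitivity analyses to assess whether the methods used to deal with missing data produce any important differences in the results". It names no methods.

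The SGRQ section fixes what the extreme values are: "A total score is calculated from 0 (no health impairment) to 100 (maximum health impairment"). The worst possible value is therefore 100 and the best is 0. The same section takes a change of 4 as the threshold for an important change. Section 2.6 makes the SGRQ, with the PGI, the primary outcome.

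**The concern.** Three features of the rule are at fault.

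1. **The values are far from the data.** An imputed 100 may lie 50 points or more from the arm mean, on a scale where 4 points matter. It then enters the comparison as an ordinary observation.

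2. **What triggers a 0 or 100 can differ by arm.** Section 2.2 gives controls no intervention, and the Discussion accepts that patients and therapist are unblinded. Adverse effects of needling can arise only under acupuncture, and setting those patients to 100 works against acupuncture. A control who leaves disappointed and is set to 100, or an acupuncture patient recorded as cured and set to 0, works for it. The direction of the bias therefore depends on who leaves and how the reason is recorded.

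3. **Two classes leave out the most useful one.** Dropout that depends on scores already observed (missing at random) has no place, although a likelihood-based mixed model handles it. Section 2.8 already names a mixed model as the analysis, but the missing-data paragraph confines it to losses completely at random.

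The cure branch also fits poorly with a disease that the Introduction describes by "chronic airflow obstruction that is not fully reversible".

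At stake is the primary result: a handful of judgements about why patients left could decide it.

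**Working it through.** **Inputs from the Protocol article.** 50 per arm, d = 0.59, alpha 5%, 20% loss in the worst case (section 2.2); SGRQ range 0 to 100 and 4-point threshold (SGRQ section).

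**Assumptions.** The documents give no SGRQ mean or SD. I take a control mean of 40 to 50 and an SD of 15 to 20, with 45 and 17 as the central case. I use a two-sided t-test at one visit as an approximation to the planned mixed model. The number of patients set to an extreme, k, is also assumed.

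**Reference point.** With d = 0.59 and 50 per arm, exact two-sided t-test power is 83.2%. (The stated 50 per arm does not reproduce once 20% loss is added: 47 per arm before loss, 47/0.8 = 58.75, so 59 after. This point does not depend on that.)

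**Shift in an arm mean.** Shift = k × (100 − arm mean)/50.

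- Arm mean 40: 60/50 = 1.2 points per patient. Arm mean 50: 50/50 = 1.0.
- Four patients of 50 (8%): 4.0 to 4.8 points, at or above the 4-point threshold.

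**Central case with a true effect.** Effect = 0.59 × 17 = 10.0, so the acupuncture mean is 45 − 10 = 35.

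- Each acupuncture patient set to 100 moves that arm by 65/50 = 1.3 points.
- Four patients move it by 5.2, so the difference falls from 10.0 to 4.8.
- The arm SD becomes √(0.92 × 17² + 0.08 × 0.92 × 65²) = √(265.9 + 311.0) = 24.0, up from 17.

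**Simulation** (40,000 trials per cell, 50 per arm, simulated scores capped at 0 and 100, k patients then set to 100). The columns under no effect give the rate of a significant result favouring acupuncture; nominal is 2.5%.

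| Control mean, SD | Power, k = 0 | 3 AT at 100 | 4 AT at 100 | No effect: 1 control | 2 controls | 5 controls |
|---|---|---|---|---|---|---|
| 40, 15 | 83% | 17% | 5% | 4% | 7% | 29% |
| 45, 17 | 83% | 29% | 14% | 4% | 7% | 23% |
| 50, 20 | 83% | 41% | 28% | 4% | 6% | 18% |

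The first and last rows are the ends of the range over the grid. Repeat runs, and whether scores are capped, move the figures by a point or so.

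**Two further cases on the same grid.**

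- Three patients at 100 in each arm: power is about 48% to 67%. Even balanced use is costly, because the SD is inflated.
- No effect and four acupuncture cures set to 0: false benefit in about 10% to 16% of trials.

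**The same dropouts left missing.** At d = 0.59 the t-test keeps 82.0% power with 47 against 50 patients and 81.5% with 46 against 50. This holds if the missing patients do not differ systematically from those observed.

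**The case against.** **The text is provisional.** It speaks of planning, gives extreme-value imputation as an example, and promises sensitivity analyses on this very question, whose details may sit in a fuller document. That softens the point but does not remove it. Extreme-value imputation is the only method named for these dropouts, it is stated separately from the sensitivity analyses, and the mixed model is expressly assigned to the other class.

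**The number of such dropouts is unknown.** This stands. The 20% loss (10 per arm) covers all reasons, and the Discussion aims to measure at least one key outcome in more than 85% of patients. Neither figure says how many losses would be classed as non-random. Three to five in one arm, all at the same extreme, is a stress case. One or two controls at 100 do little under no effect.

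**The approximation is crude.** This also stands. In a repeated-measures model a patient who leaves late still contributes baseline and week-8 data, so the exact figures would differ.

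**Scoring failure as a bad outcome can be deliberate.** A composite outcome can define failure as the worst score. The text does not present it that way: it offers the rule as a treatment of missing data.

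**Stronger readings that the documents do not support.**

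- A reader might infer that controls cannot drop out for lack of efficacy, so that the penalty falls almost wholly on acupuncture. The class is defined without reference to arm, and an unblinded control who is not improving could be placed in it.
- A reader might infer that single imputation makes the standard errors falsely small. That is not shown: here the extreme values widen the SD.
- The cure branch does no harm if it is never used.

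**Conclusion.** The point holds as a badly chosen rule for the primary comparison. Scale-limit values for dropouts judged non-random can bias the SGRQ result in either direction, and the two-class scheme leaves no place for dropout that depends on observed scores. Under the stated assumptions, three or four acupuncture patients set to 100 take most of the planned power, and five controls set to 100 raise the false-benefit rate to roughly seven to twelve times its nominal level (18/2.5 to 29/2.5). These sizes rest on an assumed SGRQ mean and SD, an assumed count of such dropouts and a single-visit test. They show what the rule can do, not what will happen. The rule should be changed before allocation is unmasked for analysis.

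**What to change.** Rewrite the missing-data paragraph:

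1. Use the likelihood-based mixed model on all observed data, under missing at random, as the main analysis whatever the reason for dropout.
2. Remove best- and worst-case imputation from the main analysis, and keep it at most as a labelled extreme bound among the sensitivity analyses.
3. Name a sensitivity analysis for non-random dropout, either delta-adjusted or tipping-point, applied by the same rule in both arms.

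The cost is one paragraph and a little extra programming. The main analysis then relies on the missing-at-random assumption, which the third step tests.
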